## Abstract

**Background:**

Stress urinary incontinence (SUI) is a common problem. In the Netherlands, yearly 64.000 new patients, of whom 96% are women, consult their general practitioner because of urinary incontinence. Approximately 7500 urodynamic evaluations and approximately 5000 operations for SUI are performed every year. In all major national and international guidelines from both gynaecological and urological scientific societies, it is advised to perform urodynamics prior to invasive treatment for SUI, but neither its effectiveness nor its cost-effectiveness has been assessed in a randomized setting.

The Value of Urodynamics prior to Stress Incontinence Surgery (VUSIS) study evaluates the positive and negative effects with regard to outcome, as well as the costs of urodynamics, in women with symptoms of SUI in whom surgical treatment is considered.

**Methods/design:**

A multicentre diagnostic cohort study will be performed with an embedded randomized controlled trial among women presenting with symptoms of (predominant) SUI.

Urinary incontinence has to be demonstrated on clinical examination and/or voiding diary. Physiotherapy must have failed and surgical treatment needs to be under consideration.

Patients will be excluded in case of previous incontinence surgery, in case of pelvic organ prolapse more than 1 centimeter beyond the hymen and/or in case of residual bladder volume of more than 150 milliliter on ultrasound or catheterisation.

Patients with discordant findings between the diagnosis based on urodynamic investigation and the diagnosis based on their history, clinical examination and/or micturition diary will be randomized to operative therapy or individually tailored therapy based on all available information.

Patients will be followed for two years after treatment by their attending urologist or gynaecologist, in combination with the completion of questionnaires.

Six hundred female patients will be recruited for registration from approximately twenty-seven hospitals in the Netherlands. We aspect that one hundred and two women with discordant findings will be randomized.

The primary outcome of this study is clinical improvement of incontinence as measured with the validated Dutch version of the Urinary Distress Inventory (UDI). Secondary outcomes of this study include costs, cure of incontinence as measured by voiding diary parameters, complications related to the intervention, re-interventions, and generic quality of life changes.

**Trial registration:**

Clinical Trials NCT00814749.

## Background

Stress urinary incontinence (SUI) is a frequently occurring problem. The Health Council of the Netherlands estimated that yearly 64.000 new patients, of whom 96% are women, consult their general practitioner because of urinary incontinence [1].

In all major national and international guidelines of professional organizations and authorities, it is advised to perform urodynamics prior to invasive treatment for SUI, e.g. the guidelines of the Dutch Urological Association, the Dutch Society of Obstetrics and Gynaecology, International Continence Society and European Association of Urology[2,3].

Usual care in the Netherlands for urinary incontinence in the general practitioners setting is an investigation by history, clinical examination and voiding diary. When there is no clear indication for urge incontinence or neurological disease, the patient will be referred for physiotherapy. In case there is no improvement the patient will subsequently be referred to the gynaecologist or urologist [4]. Patient history and clinical examination are important aspects of the assessment of patients that suffer from stress urinary incontinence. Patient history is quantified by using parameters based on validated questionnaires and a voiding diary for 1 to 2 days. The most common surgical therapy for SUI is the midurethral sling procedure of which the tension free vaginal tape (TVT) was first introduced. These slings have an average success rate of 90% [5].

Urodynamics do not generate major morbidity but are generally considered as unpleasant by the patients, and inhere a risk of urinary tract infections as high as 20% [6]. Urodynamics try to enhance the understanding of lower urinary tract functioning and reveal the underlying pathology that cause patients complaints. It is an extension of patient history and physical examination in an unphysiological setting.

The assumption is that the urodynamic setting is capable of making a distinction between several pathophysiological mechanisms causing the same micturition symptoms. If this holds true, the outcome of the available treatment options derived from the urodynamic based diagnosis would be better than treatment based on diagnosis made without urodynamics. However, the urodynamic investigations that differentiate between several types of SUI and specify for the type of operation, lack validation and predictive value in individual cases [7].

Moreover, since the introduction of easy to administer midurethral polypropylene slings, a simplified reasoning has found ground that states that every type of SUI is treated in the same way and therefore no urodynamic investigation would be needed.

The value of urodynamics has never been the specific subject of a randomized controlled trial [8]. Several studies have evaluated the value of urodynamics indirectly.

A retrospective cohort study on TVT has concluded that urodynamics do not have a predictive value on outcome after midurethral sling surgery [9]. In a randomized controlled trial on Burch compared with pubovaginal sling procedure, the predictive value of urodynamics was evaluated. Findings on urodynamic investigation did not seem to predict stress continence outcome [10].

The subjective and objective outcome of surgical intervention with or without preoperative urodynamic investigation has not been compared, with the exception of one retrospective study on colposuspension and one cohort study on TVT [11,12]. In these two studies no differences were found between the groups with and without urodynamics.

The strong conclusion from the Cochrane Review on the value of urodynamics was that a randomized trial is needed [13].

Thus, the role of urodynamics in the objectivation of SUI in women is nowadays questionable and very much under debate. In 25–30% of the women the symptom of SUI is not demonstrable probably due to the artificial situation during the investigation [5].

If urodynamics are not needed to diagnose types of SUI, this could be to prevent complications of surgery such as an overactive bladder. However in almost half of the patients with overactive bladder symptoms, there are no abnormal detrusor contractions visible on urodynamics [14]. On the other hand detrusor contractions during urodynamics that are regarded as the proof for overactive bladder complaints, can be seen in 20% of women without symptoms of an overactive bladder [15]. It is therefore questionable, whether it can predict the therapeutic effect as well as the risk of complications, like de novo urgency or aggravation of urgency and urinary retention [7,8].

The introduction of minimally invasive techniques for SUI therapy, such as the midurethral tension free tape procedure, has led to an enormous increase in the number of operations in the Netherlands. In 1999, 1,600 operations were performed. This number has increased to over 4,000 in 2003 and is expected to be 5,000 by today [16].

### Economic relevance

We estimate that two thirds of all women with symptoms of SUI who had urodynamics will proceed to surgery and one third will be given another non-surgical intervention which is usually medication. From this calculation it appears that for this indication urodynamics are performed approximately 7500 times per year in the Netherlands.

At expected costs of about 300 euro per test, urodynamics stand for 2.25 million euro health insurance charges.

In case urodynamics would be omitted, costs of possible extra complications are foreseen. We estimate a maximum of 10% additional urgency complaints [17,18]. Antimuscarinic treatment is available but has a record of only short time usage in almost all patients, and thus the costs are limited [19]. The other possible complication is urinary retention or voiding dysfunction. This occurs in less than 5% of patients after colposuspension, but is less in tension free midurethral slings and is supposed not to change with or without urodynamics [20]. This therefore will not have major financial impact on the outcome. Possible further additional costs are costs related to reoperation (repositioning of the sling estimated at 0.5–1%), and outpatients' costs.

In conclusion, it is likely that urodynamics do not have a role in the quality of care for women with SUI and that urodynamic testing in women with SUI is not cost-effective.

For this study our hypothesis was that there is no difference between outcome of surgery and individually tailored therapy in women with a discrepancy between urodynamic findings and findings from other investigations, such as history and clinical examination. In case of confirmation of this hypothesis, urodynamic investigation in women with predominant SUI could be safely omitted.

## Methods/design

The primary aim of the VUSIS study is to evaluate whether urodynamic testing is effective in patients with symptoms of SUI in whom surgical treatment is considered

The VUSIS is a multidisciplinary, multicentre diagnostic cohort study with a randomized controlled trial (RCT) embedded. All women with symptoms of predominantly SUI in whom surgical treatment is considered will undergo urodynamic investigation. Only women with a discordant finding compared to history and physical examination will be randomized. Patients with concordant urodynamics will be registered [see figure 1].

**Figure 1 F1:**
[figure not shown]
**Summary of trial design**.

The study has been approved by the institutional review board of the Radboud University Nijmegen Medical Centre, in Nijmegen. Ethical approval for this study has been obtained on 02-10-2008, number 2006/197.

Eligible patients will be identified by gynaecologists and urologists from participating hospitals in the Netherlands [see Additional file 1]. All women presenting with SUI where conservative therapy (i.e. physiotherapy) has failed and surgical therapy is considered, will be asked for permission of registration in the study. SUI must have been demonstrated on physical examination and/or micturition diary. Patients will be excluded in case of previous incontinence surgery, in case of pelvic organ prolapse 1 centimeter beyond the level of the hymen and/or in case of residual bladder volume of more than 150 ml on ultrasound or catheterization [see figure 2].

**Figure 2 F2:**
[figure not shown]
**Study inclusion and exclusion criteria**.

In all patients the following items will be recorded at inclusion:

1. History and clinical examination

2. 48 h-Bladder (voiding and incontinence) diary

3. Validated Quality of Life questionnaires (Short Form 36, Euroqol 5D, Urinary Distress Inventory, Incontinence Impact Questionnair, Defecatory Distress Inventory)

4. Urinalysis for the detection of urinary tract infection

5. Residual urine measured by ultrasound

All women will undergo urodynamic investigation. Urodynamics will be performed according to International Continence Society standards and consists of free flow and measurement of residual, provocative filling cystometry with abdominal leak point pressure measurement, pressure flow study and a urethral pressure profilometry in rest and during stress[21]. The outcomes will be matched with urodynamic findings to assess the potentially useful parts of the urodynamic findings. Postoperative urodynamics is not part of the study.

When the result of the urodynamics does not confirm the history of SUI, or shows relative contra-indications for operation, the investigation is called discordant. Whether a test result is discordant is decided by the attending urologist or gynaecologist. Figure 3 demonstrates the various reasons for discordancy.

**Figure 3 F3:**
[figure not shown]
**Discordant findings on urodynamic investigation**.

Women with discordant findings on urodynamics will be approached to participate in the randomized controlled part of the study.

After they have given informed consent, the patients with discordant test results at urodynamics are randomly assigned to the study or control group. In the study group, the decision for intervention will be based on history and clinical examination only, which will be surgical treatment; a midurethral sling. The choice for the kind of procedure is left to the discretion of the attending doctor. In the control group the decision for therapy will be based on history and clinical examination in combination with the result of the discordant findings on urodynamics. This includes medical treatment, prolonged physiotherapy, pessary treatment, but also surgical treatment can be one of the chosen therapies.

All women with SUI, who present at one of the participating hospitals, will be referred to a gynaecologist, urologist or a specifically appointed research nurse for counselling. Eligible women will receive an information sheet. Once women with discordant test results have given consent for the trial, they are randomized through a website, according to a computer-generated randomization sequence. Stratification will be applied for centre. Randomization will be 1:1 for operative treatment and individual treatment.

Patients in the RCT will be followed up from trial entry until the end of the study (anticipated average: two years). Follow-up is composed of the same items as recorded at inclusion.

After six weeks, six, twelve and twenty-four months patients will visit their attending gynaecologist or urologist. Physical examination will be performed and consists of detection of erosions, stress test for urinary leakage, and measurement of the residual volume. The patients will complete the questionnaires at all moments of follow-up.

After the intervention additional therapy is possible in both arms and will be recorded in the Case Record Form.

The cohort group will receive the same questionnaires once, at one year after the intervention.

### Patient outcome measures

The primary outcome of this study is clinical improvement of incontinence as measured with the validated Dutch version of the UDI.

Secondary outcomes of this study include costs, cure of incontinence as measured with voiding diaries, complications such as re-operation or overactive bladder symptoms, and quality of life.

The trial results will be incorporated in a diagnostic model to compare the current strategy (urodynamic evaluation in all patients) with the alternative strategy (immediate TVT surgery without urodynamic evaluation).

The study design will enable us to compare the costs and effects of the following strategies:

I. Immediate midurethral sling without preceding urodynamic evaluation.

II. Urodynamic evaluation in all patients and midurethral sling depending on urodynamic evaluation results.

III. Sequential or probabilistic combinations, based on the prior probability of the fact that the urodynamic evaluation will change management.

### Sample size considerations

The primary outcome of this study is the improvement of UDI at 12 months after baseline. The power calculation is performed using the non-inferiority assumption. The calculation is based on registration of 600 patients in the cohort study, of whom 200 will have discordant findings. When approximately 50% of the women give informed consent for randomization, 102 women with discordant findings will be randomized (51 to each group). As based on the non-inferiority assumption, the mean improvement in UDI in both groups is expected to be 35 with standard deviation of 10. A difference in mean improvement of 5 or less is considered as non-inferior (power 80% using one-sided testing at 0.05).

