### Statistical analysis

Multivariate analysis of covariance with group, centre and the baseline covariate as independent variables will be used to estimate differences in improvement of the UDI after 12 months between the groups with 95% confidence intervals. As the UDI data are likely to be skewed, data will be log transformed prior to analysis. Other variables (i.e. IIQ) will be analyzed similarly.

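### The 102 women to be randomised are also the number needed for analysis, so the stated 80% power leaves almost no room for missing 12-month UDI forms

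*Protocol article*

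**What the plan says.** Under Sample size considerations, the protocol article takes the improvement in UDI at 12 months as the primary outcome and goes from 600 registered women to 200 with discordant findings. It continues: "When approximately 50% of the women give informed consent for randomization", then "102 women with discordant findings will be randomized (51 to each group"). The inputs follow. For the expected outcome, "the mean improvement in UDI in both groups is expected to be 35 with standard deviation of 10". For the margin, the wording is: "A difference in mean improvement of 5 or less is considered as non-inferior". The error rates appear in brackets: "power 80% using one-sided testing at 0.05". No step after randomisation reduces the number.

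Under Methods/design (the text after Figure 3), women in the randomised part are seen at six weeks and at six, twelve and twenty-four months, and "The patients will complete the questionnaires at all moments of follow-up". The UDI is one of the questionnaires listed at inclusion, and follow-up repeats the same items.

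Under Statistical analysis, a covariance model with group, centre and baseline is used "to estimate differences in improvement of the UDI after 12 months between the groups". The article describes no role for the other visits in that estimate.

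**The concern.** A power statement describes the women who are analysed, not those who are randomised. If the two numbers are the same, the plan assumes that practically every form comes back. That is a demanding assumption here. The outcome is a patient-completed questionnaire one year on, in a trial run across about 27 hospitals. The arms are a midurethral sling and individually tailored therapy, so women will generally know what they received.

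The trial is meant to support omitting urodynamics if surgery is shown to be non-inferior. With lower power than stated, an inconclusive result becomes more likely even if the hypothesis of no difference is true. Loss that differs between the arms could also bias the comparison in either direction.

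**Working it through.** **Inputs** (Sample size considerations, except allocation)

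- True difference in mean improvement: 0 (35 in both groups)
- Standard deviation: 10
- Non-inferiority margin: 5
- Alpha: 0.05, one-sided; power 80%
- Allocation: "Randomization will be 1:1 for operative treatment and individual treatment" (Methods/design)
- Loss after randomisation: none stated

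**Step 1. Reproduce the plan's figure.** By the normal approximation,

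n per group = 2 × [SD × (z₀.₉₅ + z₀.₈₀) / margin]² = 2 × [10 × (1.645 + 0.842) / 5]² = 49.5, rounded up to 50.

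With the t distribution, power is P(T > t₀.₉₅,df), where T is noncentral t with df = 2n − 2 and noncentrality 5 / (10 × √(2/n)):

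| n per group | Noncentrality | Power (t) | Power (normal) |
|---|---|---|---|
| 49 | 2.475 | 79.2% | 79.7% |
| 50 | 2.500 | 79.9% | 80.4% |
| 51 | 2.525 | 80.6% | 81.1% |

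So 51 is the smallest equal group size that reaches 80% by the t calculation. It matches the plan's figure exactly, with zero loss.

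**Step 2. Look for an allowance.** The 50% consent rate takes about 200 discordant women to about 100 randomised. It acts before randomisation and cannot cover forms missing afterwards. The slack is the gap between 51 and 50 per group, which is about two women of 102.

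**Step 3. Power after loss.** The article gives no loss rate, so the rates below are assumptions. Numbers analysed are 51 × (1 − loss), rounded.

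| Assumed loss | Analysed per group | Unadjusted power (t) |
|---|---|---|
| 0% | 51 | 80.6% |
| 10% | 46 | 76.9% |
| 15% | 43 | 74.4% |
| 20% | 41 | 72.6% |

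**Step 4. What baseline adjustment might recover.** If baseline UDI has correlation r with improvement, the residual standard deviation is 10 × √(1 − r²). The article gives no r, so a range is shown (t-based power, one degree of freedom spent on baseline):

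| Analysed per group | r = 0.2 | r = 0.3 | r = 0.4 | r = 0.5 |
|---|---|---|---|---|
| 46 | 78% | 80% | 83% | 86% |
| 43 | 76% | 78% | 81% | 84% |
| 41 | 74% | 76% | 79% | 83% |

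Spending about 26 further degrees of freedom on centre lowers these by less than half a percentage point; imbalance within centres is not modelled.

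**The case against.** The best defence is that the planned analysis is more efficient than the one powered. The Statistical analysis section adjusts for baseline, and the last table shows that a correlation of 0.3 to 0.4 would absorb a loss of 10% to 15%. This stands as a possibility. However, the sample size section neither states a correlation nor relies on one, so the stated 80% remains a figure for an unadjusted comparison with practically complete data. The defence also rightly notes that every loss rate used here is assumed.

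Three stronger readings are tempting, and the article does not support them.

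- *The plan discards women without a 12-month form.* A model of 12-month improvement has no outcome for such a woman unless a value is imputed. But the article states no complete-case rule, and the handling of missing data may be in an analysis plan that is not shown. That silence is not a fault here.
- *The power claim fails with any loss at all.* There is slack of about two women: with 50 per group, power is 79.9% by t and 80.4% by the normal approximation.
- *The shortfall is much larger because results are reported with 95% confidence intervals.* Judging non-inferiority on a two-sided 95% interval would correspond to one-sided 0.025, where 51 per group give 70.6% with no loss at all. That drop comes from the alpha level. It is a separate matter and should not be counted as an effect of attrition.

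Finally, covariance analysis at one prespecified time point is a valid primary analysis. The longitudinal model proposed below is an improvement, not the correction of an error.

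**Conclusion.** The point holds in a limited form. The article uses 51 per group both as the number randomised and as the number needed for analysis, and it makes no allowance for loss after randomisation. The stated 80% survives only if about two women or fewer lack the 12-month UDI. At 10% to 20% loss, the fall in unadjusted power is about 4 to 8 percentage points (80.6% to 76.9%, and to 72.6%).

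This rests on the article's own standard deviation, margin and alpha, on equal loss in the two groups, and on the assumed loss rates. The true shortfall may be smaller if baseline UDI predicts improvement. The uninflated number itself is certain from the article's figures; the size of the consequence is conditional.

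**What to change.** 1. In Sample size considerations, label 102 as the number randomised. State the expected loss by 12 months and the power at the number then analysed, for example about 74% at an assumed 15% loss (43 per group). If baseline adjustment is to be counted on, state the correlation assumed and its source.

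2. In Statistical analysis, estimate the 12-month group difference from a longitudinal mixed model of the UDI at 6 weeks and 6, 12 and 24 months, with baseline UDI, centre, visit, group and group-by-visit. The 12-month contrast stays primary. Centre must stay in because it is the randomisation stratum and already a planned covariate. Say how the planned log transformation carries over. Women without a 12-month form but with other follow-up forms then contribute, under the usual missing-at-random assumption.

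The cost is a less favourable stated power and slightly more analysis work. No extra patients or visits are needed, since these forms are already collected.

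Neither change by itself guarantees 80%. Keeping 102 women analysable would mean randomising 102 / 0.90 = 113.3, so 114, at 10% loss, or 102 / 0.85 = 120 at 15% loss, with recruitment enlarged to match.

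### The sample size rests on a one-sided 5% non-inferiority test, but the analysis section plans 95% confidence intervals and does not link them to that test or to the margin

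*Protocol article*

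**What the plan says.** Under Sample size considerations, the Protocol article states: "The primary outcome of this study is the improvement of UDI at 12 months after baseline". It continues: "The power calculation is performed using the non-inferiority assumption". The inputs follow: "the mean improvement in UDI in both groups is expected to be 35 with standard deviation of 10", and "A difference in mean improvement of 5 or less is considered as non-inferior", with "power 80% using one-sided testing at 0.05". The resulting size is 102 randomized women, 51 per group.

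Under Statistical analysis, the article plans an analysis of covariance with group, centre and baseline as independent variables, to estimate "differences in improvement of the UDI after 12 months between the groups with 95% confidence intervals". It adds that the data will be log transformed because skewness is expected. The section mentions no one-sided test, no 90% interval and no comparison of an interval limit with the margin of 5. It also does not say whether the 95% interval is one-sided or two-sided.

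**The concern.** A non-inferiority test at one-sided 5% is the same as asking whether one limit of a two-sided 90% interval (equivalently, a one-sided 95% bound) clears the margin. A conventional two-sided 95% interval implements the stricter one-sided 2.5% test. The article therefore gives one level for sizing and another for the only inferential output it describes, and nothing connects them.

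Readers will naturally hold the reported 95% interval against the margin. A result that clears the margin on the 90% limit but not on the 95% limit could then be called either way once the data are known. The Economic relevance section says that confirming the hypothesis would justify leaving out urodynamics in women with predominant SUI, so the threshold for that claim should be fixed in advance.

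**Working it through.** **Inputs (Protocol article, Sample size considerations):** margin 5 UDI points; SD 10; expected improvement 35 in both groups, so a true difference of 0; 51 per group; power 80%; one-sided 0.05. Allocation is 1:1 (Methods/design, text after Figure 3). The 95% level comes from Statistical analysis; reading it as two-sided is an assumption based on convention.

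**Step 1: reproduce the stated size.** Normal approximation, per group:

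n = 2 × (z_α + z_0.80)² × SD² / margin² = 2 × (1.645 + 0.842)² × 100 / 25 = 49.5, so 50.

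The noncentral-t calculation gives 51, the stated figure.

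**Step 2: power with 51 per group.**

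- SE = 10 × √(2/51) = 1.98, and margin/SE = 5/1.98 = 2.525.
- One-sided 0.05: Φ(2.525 − 1.645) = Φ(0.880) = 81.1%; noncentral t with 100 df gives 80.6%.
- One-sided 0.025: Φ(2.525 − 1.960) = Φ(0.565) = 71.4%; noncentral t gives 70.6%.

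The chance of failing to show non-inferiority when the arms are equal is therefore about 19% under the first rule and 29% under the second.

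**Step 3: size for 80% power at one-sided 0.025.** n = 2 × (1.960 + 0.842)² × 100 / 25 = 62.8, so 63 per group, or 64 by noncentral t. That is 126 to 128 women, against the planned 102. This only shows the scale of the gap; it is not a call for more patients.

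**Step 4: where the two rules disagree.** With SE 1.98 and 100 df, the half-widths are about 3.29 (90%) and 3.93 (95%). With improvement taken as study minus control and the lower limit compared with −5:

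- the 90% interval passes if the observed difference is above −5 + 3.29 = −1.71;
- the 95% interval passes if it is above −5 + 3.93 = −1.07.

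An observed difference between −1.71 and −1.07 passes under one rule and fails under the other. If the arms are equal, this happens with probability 80.6% − 70.6% = 10.0%, about one trial in ten.

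**Step 5: sensitivity.** If 27 centres enter as fixed effects, the error df fall to 102 − 2 − 26 − 1 = 73, and power is 80.4% and 70.2%, almost unchanged. Losing two women per group (49 analysed) gives 79.2% and 68.8% by noncentral t, so 51 leaves almost no slack even under the stated test.

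**The case against.** The strongest reply is that the article contains no outright contradiction. The sample size section names the test. The analysis section uses the language of estimation and never says that non-inferiority will be judged from the 95% interval. A one-sided 5% test reported beside a descriptive 95% interval is coherent, and a one-sided 95% bound would match the sizing exactly, with power still about 81%. This stands: the 71% is conditional on a rule that the article does not state. A reader might infer that the sample size was miscalculated, or that the trial's real power and error rate differ from those stated. The documents support neither inference, because 51 per group is right for the stated test.

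It can also be said that 71% is not the power of the planned analysis, which adjusts for baseline. That is true. As an illustration only, with equal variances and a baseline-to-12-month correlation of 0.5 (assumed; the article gives none), the variance of the adjusted difference is (1 + 0.5)/2 = 0.75 of the unadjusted one. The SE becomes 1.98 × √0.75 = 1.715, and power at one-sided 0.025 becomes Φ(5/1.715 − 1.960) = Φ(0.955), about 83%. Loss to follow-up works the other way, and the sample size section mentions no allowance for it.

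Finally, the detailed decision rule may sit in an analysis plan that is not shown. Its absence here is not the point. The point is that two levels which the article does state do not match, and a reader has no way to tell which one governs.

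**Conclusion.** The point holds as a moderate inconsistency between sizing and analysis. The sample size is correctly calculated for a one-sided 5% test. If non-inferiority is instead read from a conventional two-sided 95% interval, power with the same 102 women falls from about 81% to about 71%, and the type I error at the margin is 2.5% instead of 5%. The trial would then be more conservative than stated, so the cost is in power, not in false claims of non-inferiority.

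These figures assume an unadjusted comparison on the raw UDI scale with SD 10, a true difference of 0 and no loss to follow-up. Baseline adjustment could raise the power and dropout would lower it.

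The planned log transformation adds a related difficulty: an interval for a difference in logs is not in UDI points, so a margin of 5 points cannot be read from it directly under either rule.

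**What to change.** Before the data are seen, align the two sections by stating one decision rule:

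- **Option (a):** conclude non-inferiority if the lower limit of the two-sided 90% interval (one-sided 95% bound) for mean improvement, study minus control, lies above −5. State that the 95% interval is descriptive. The stated 80% power then stands.
- **Option (b):** decide on the two-sided 95% interval and restate the power for 102 women as about 71%, with the assumptions behind that figure.

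Under either option, say that the comparison with the margin is made on the UDI-point scale on which the 5 is defined, and keep any log-scale analysis as supportive.

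The cost is wording only, with no extra patients or data collection. Option (b) also means publishing a less favourable power figure.
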